### Methods in analysis to handle protocol non-adherence and any statistical methods to handle missing data {20c}

All participants will be included in the main analysis (intention to treat) regardless of dropout or adherence to the intervention. Only those who withdraw from the study and all their collected data will be excluded from the analysis. Missing data on the secondary outcomes will be handled by multiple imputation if missingness is found to be “completely at random” and > 10%.

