#### Secondary outcome measures

Self-reported levels of suicidality, depression, anxiety, stress, resilience, problem-solving skills, and self- and therapist-reported level of therapeutic engagement are measured. Scores will be compared for each group at each follow-up time point. A cost comparison will also be done for both interventions (compared to TAU), and estimates will be based on service information regularly collated by GCMHSS and ED (e.g. contact hours, bed stays, ED visits). We expect a low completion rate (see the “Sample size” section). Study completion will be analysed post hoc, as a secondary outcome.

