### Sample size {14}

The sample size was calculated on the basis of a time to event analysis of the time to representation for suicidality. From previous studies using CBT as an additional treatment component following attempted suicide [24, 39], we anticipated that the proportion of patients re-presenting for attempted suicide over a 2-year follow-up period will be approximately half that of the TAU group. From recent data from our health service, this represents a decrease from 48 to 24%. To detect this difference (equivalent to a hazard ratio of 0.42) by the log rank test in a proportional hazards time-to-event analysis with 80% power at a two-sided significance level of 5%, we require 132 participants in two groups of 66 each. However, we anticipated a dropout rate of approximately 4.5% per month which would result in 35% of participants completing the full 24-month follow-up (65% total dropout). The effective dropout rate is thus 41%, as those dropping out later contribute proportionately more. When accounting for this dropout rate, to maintain the same power, a total of 137 participants in each of the three cohorts are required for a total of 411 in total.

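### The missing-data rule for the secondary outcomes is inverted: it imputes only if missingness is found to be completely at random, and names no method otherwise

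*Protocol article*

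**What the plan says.** The section on non-adherence and missing data {20c} sets one rule for the psychometric scales: "Missing data on the secondary outcomes will be handled by multiple imputation if missingness is found to be" "completely at random" and exceeds 10%. Both conditions must hold. It does not say what happens if they do not.

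Secondary outcome measures describes the comparison in one line, "Scores will be compared for each group at each follow-up time point", and warns that "We expect a low completion rate". Plans for assessment and collection of outcomes {18a} places the assessments at baseline, end of intervention, 6, 12 and 24 months.

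Sample size {14} gives the expected loss: "we anticipated a dropout rate of approximately 4.5% per month", with "35% of participants completing the full 24-month follow-up (65% total dropout").

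The mixed-effects models in Statistical methods {20a} are assigned to time to re-presentation, not to the scales.

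**The concern.** A rule on missing data should bring in a correction where the observed scores may mislead. This one does the reverse.

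- **Under MCAR**, those with scores are a random subset of those randomised. The unadjusted complete-case comparison is unbiased, so imputation is optional.
- **Under MAR**, for example when dropout depends on arm and on earlier scores, complete cases can be biased. Imputation with the right predictors, or a likelihood-based model, can correct this. Here the rule switches imputation off.

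The trigger is also unworkable. A test can fail to reject MCAR, but that does not show that MCAR holds.

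At stake are the between-arm comparisons of suicidality, depression, anxiety, stress, resilience and problem-solving, in a trial that expects heavy loss. The method would also be chosen after looking at the missingness pattern.

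**Working it through.** **1. The plan's dropout figure.** Input: 4.5% per month over 24 months (Sample size {14}).
- Compounded: 1 − 0.955^24 = 66.9%.
- As a constant hazard: 1 − exp(−0.045 × 24) = 66.0%.
- Stated: 65%. The figure reproduces, given that the monthly rate is called approximate. Working back, 0.35^(1/24) = 0.957, or about 4.3% per month.

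**2. Missingness by visit**, assuming that dropout applies to the questionnaires:

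| Visit | 1 − 0.955^m | 1 − 0.35^(m/24) |
|---|---|---|
| 6 months | 24% | 23% |
| 12 months | 42% | 41% |
| 24 months | 67% | 65% |

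At 24 months, 0.35 × 137 = 48 per arm would have scores. Loss reaches 10% at ln(0.9)/ln(0.955) = 2.3 months. The threshold is therefore passed at 6, 12 and 24 months, and there the MCAR finding alone decides whether imputation is used. The end-of-intervention visit has no calendar time in the article, so this cannot be said of it.

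**3. What imputation adds under MCAR.** Simulation with 137 per arm, 65% missing at the last visit and a true effect of −0.30 in the units of the simulated score. Mean estimates: complete cases −0.31 unadjusted and −0.30 baseline-adjusted; multiple imputation −0.31. The spread (SD) of the estimate is 0.143 for baseline-adjusted complete cases and 0.132 with imputation. There is no bias to remove and a small gain in precision.

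**4. What is lost when dropout depends on the score.** All parameters here are assumptions; the documents give none. Standardised scores, no true effect, correlations 0.6 (baseline with 12 months) and 0.7 (12 with 24 months). The log-odds of having a 24-month score are −0.65 − b × (12-month score), with b = 0.4 in one arm. About 35–38% are retained and every 12-month score is observed. False difference in SD:

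| b in the other arm | Complete cases | Complete cases, baseline-adjusted | MAR analysis using baseline and 12 months |
|---|---|---|---|
| 0.4 | 0.00 | 0.00 | 0.00 |
| 0.8 | 0.14 | 0.09 | 0.00 |
| 1.2 | 0.23 | 0.15 | 0.00 |

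**5. The same with 12-month scores also lost.** About 58% attend at 12 months, attendance depends on the 12-month score itself, and somewhat under 40% remain at 24 months. With b = 0.8 and 1.2 in the second arm, complete cases are off by about 0.15–0.24 SD. The MAR analysis is still off by about 0.06–0.12 SD, so it removes about half.

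**The case against.** The strongest reply is that the rule is badly worded but that its consequences can be overstated. Several parts of that stand.

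- **Fallback.** A reader might infer that the plan prescribes a complete-case analysis without baseline scores. It does not. It is silent, and model form and covariates are details that an article commonly leaves to the full protocol or SAP. What stands is that the stated trigger is inverted and nothing is stated for other missingness.
- **MCAR as the only safe case.** A reader might infer this too. It is too strong: a covariate-adjusted complete-case analysis is also unbiased if missingness depends only on covariates in the model.
- **A third of participants.** It is tempting to say that every psychometric result would rest on about a third of those randomised. That holds at 24 months only; about 76% remain at 6 months and 58% at 12 months.
- **Differential dropout.** It is plausible, because two arms receive therapy sessions and ASSIP adds letters over 24 months. It is not documented. SPP has its own structured follow-up, and the research assistant's contact for questionnaires is described without distinction by arm. With equal dependence in both arms the simulated bias is zero.
- **Reach.** The primary outcome comes from ED records, and all participants stay in the main analysis regardless of dropout.

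None of this rescues the rule. It is an explicit decision rule and not an omitted detail, and no other section repairs it.

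**Conclusion.** The point holds as a wrong rule for the secondary outcomes. The inversion follows from the definitions of MCAR and MAR and needs no simulation. The plan's own dropout rate makes the MCAR condition decisive at 6, 12 and 24 months.

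The size of the harm is uncertain. Under the assumed mechanisms, complete cases show a false difference between 0.00 SD (equal dependence on severity) and about 0.14–0.24 SD (dependence two to three times as strong in one arm). A MAR analysis removes this when interim scores are observed, and about half of it when interim scores are also lost according to their own value. A MAR method is therefore the better default but no guarantee, which is why a sensitivity analysis is needed.

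This should be fixed. It does not threaten the primary result.

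**What to change.** Delete the completely-at-random condition in {20c}. State that missing secondary scores are handled under missing at random, whatever an MCAR test shows, by one of two methods named in advance:

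- a repeated-measures mixed model for each scale, with arm by time and the baseline score; or
- multiple imputation by arm, with baseline and all interim scores in the imputation model.

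Add a not-at-random sensitivity analysis, for example delta-adjusted imputation, because of the loss expected by 24 months. Settle the wording before outcome data are examined.

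The cost is analysis wording and modest programming. The scores needed are already scheduled for collection, and the sample size does not change.

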### Plans to give access to the full protocol, participant level-data, and statistical code {31c}

We plan to make de-identified aggregate data available, in keeping with relevant privacy policy and considerations and subject to a formal agreement with the requesting institution.

### Oversight and monitoring

#### Composition of the coordinating centre and trial steering committee {5d}

##### Steering committee (CIs based at GCUH)

Study design and conception, preparation of protocol and revisions, organising working group meetings, reporting to clinical governance, recruitment, data collection, and dissemination of findings.

##### International collaborators (subgroup)

Expertise assessment training (CIs KM, AP), ASSIP training, data analysis, and dissemination of findings.

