#### Implementation {16c}

The RA is responsible for the recruitment of participants and for the assignment of participants to intervention arms. The RA enables the treatment pathway by booking an appointment for the appropriate intervention and informing the ASSIP-CBT Clinician (adult > 25 or youth clinician 16–25, as applicable). The allocation sequence is generated by a biostatistician who is not involved in the recruitment or assessment of participants. Clinical processes and interventions, consumer assessment/documentation, and treatments as well as follow-up, are not affected by the recruitment to the ASSIP-CBT study and are progressed by treating teams as clinically appropriate, as per usual practices.

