### Assignment of interventions: blinding

#### Who will be blinded {17a}

Given the clear differences in the therapy interventions, participants and those administering the interventions are not blinded. However, those assessing the outcomes will be blinded to group assignment.

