#### Procedure for unblinding if needed {17b}

Not applicable, as those responsible for the healthcare of the participant are not blinded to the group assignment and can inform the statistician to remove data related to a participant with a particular participant number.

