## Statistical methods

### Statistical methods for primary and secondary outcomes {20a}

To determine the effectiveness of additional CBT + SPP or ASSIP+SPP compared with SPP alone, univariate (log rank test) and multivariate Cox proportional hazard shared frailty regression models and multilevel mixed effects parametric models will be used to analyse time to re-presentation for suicide attempts [35]. Time to suicide attempt is measured by calculating the total number of days from the initial presentation (with days of psychiatric admission for some consumers taken into account), to the re-presenting date for a subsequent suicide attempt and may include multiple representations [35]. For participants without a subsequent suicide attempt, the total number of days from enrolment to the last assessment (24 months) will be calculated. All collected demographic and clinical variables will be considered in the model-building process. Variables with *P* ≤ 0.1 on univariate analysis will be included in all combinations and retained in the model if *P* < 0.05. Plausible interactions of retained variables will be tested. Collinearity of potential model variables will be assessed using the variance inflation factor. Where appropriate, the proportional hazards assumption will be tested using Schoenfeld residuals. Kaplan-Meier plots will allow visual comparisons between the groups. Analyses will be undertaken on an intention to treat basis. Stata 15 (Stata Corp. College Station, TX, USA) will be used for statistical analyses.

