Another potential limitation could be the therapist’s allegiance to a particular type of therapy or therapy model [18]. There may also be differences in therapists’ skills and competencies between the two therapies. Clinicians in this study are delivering both the ASSIP and the Brief CBT for Suicide Prevention (and have received training for both). The steps we have taken to reduce this potential bias include providing opportunities for supervision (that directly addresses any therapy adherence or allegiance issues) and the application of an ASSIP therapy adherence scale [62]. In addition, both models are manualised, so this should mitigate any therapist biases. Finally, it is possible that participants may seek to represent in some other setting, and therefore, we will not capture them in our data records. Examples are people who may present interstate (our service is located close to a state border) or who might present to a primary healthcare provider. The study is being conducted in a “real world” setting; as such, we follow a pragmatic approach in terms of what can and cannot be controlled for.

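### One subgroup is given both ASSIP training and data analysis, and stated blinding covers outcome assessors only, so the allegiance bias the protocol raises is guarded for therapists but not for analysts

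*Protocol article*

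**What the plan says.** Only the protocol article is at hand.

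- **Roles.** Under International collaborators (subgroup), the listed functions include "ASSIP training, data analysis, and dissemination of findings". The entries for the steering committee, the working group and the supervision and MDT groups do not mention data analysis.
- **Blinding.** Who will be blinded {17a} says that "participants and those administering the interventions are not blinded" and that "those assessing the outcomes will be blinded to group assignment". The Methods part of the Abstract and Trial design {32} also name outcome assessors only.
- **Statisticians.** Implementation {16c} states: "The allocation sequence is generated by a biostatistician who is not involved in the recruitment or assessment of participants". Procedure for unblinding if needed {17b} adds that staff who know the allocation "can inform the statistician to remove data related to a participant with a particular participant number". Neither section says who runs the outcome analysis.
- **Analysis.** For time to re-presentation, Statistical methods {20a} says that "univariate (log rank test) and multivariate Cox proportional hazard shared frailty regression models and multilevel mixed effects parametric models will be used". Every demographic and clinical variable collected is a candidate covariate, screened at P of 0.1 or below and kept below 0.05. Interactions considered plausible are then tested.
- **Allegiance.** Limitations names the therapist's "allegiance to a particular type of therapy or therapy model" as a possible limitation. The countermeasures are supervision, an ASSIP adherence scale and manualised therapies.

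**The concern.** Allegiance can act at two points: when therapy is delivered, and when the results are analysed. The protocol guards the first. At the second, it places analysis in the group that trains one of the two therapies and states no masking there.

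This would matter little if the primary analysis were a single fixed procedure. It is not: several model families are admissible, and some modelling decisions wait for the data. If the arms are visible when those decisions are made, a preference for ASSIP could influence, even unintentionally, which model is reported or which interaction is pursued. The contrast chiefly at stake is ASSIP + SPP versus SPP alone, one of the two main comparisons under Objectives {7}. ASSIP against CBT is labelled exploratory under Hypotheses.

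**Working it through.** No figure in the plan underlies this point, so the check sets the sections side by side.

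**1. Who analyses?** Of the four groups described under the trial's governance, one is given data analysis: the international collaborators. The steering committee has data collection and dissemination, and all subgroups report to it. The assignment is therefore stated, not inferred.

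**2. Does the same entry include ASSIP training?** Yes. It is a list for a subgroup. One item, assessment training, is tied to particular investigators; the other items are not. The list neither shows nor rules out that trainers and analysts are the same people.

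**3. Is the analyst masked?** Section {17a} places participants and those giving the interventions on the unblinded side and outcome assessors on the blinded side. The analyst is on neither. Section {17b} opens a channel from unblinded staff to the statistician by participant number; it neither discloses the arm nor bars its disclosure. De-identification under Confidentiality {27} hides the person, not the arm.

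**4. How much is left to judgement?**

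| Element of {20a} | Fixed or open |
|---|---|
| Intention-to-treat basis | Fixed |
| Log-rank test, also the basis of the sample size {14} | Named, but not declared primary |
| Covariate thresholds (0.1 to enter, below 0.05 to stay) | Fixed rule, applied to trial data |
| Log-rank, frailty Cox or parametric mixed model as the reported result | Open |
| Which interactions are plausible | Open |

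The last row has consequences: Methods for additional analyses {20b} says significant interactions will be used to suggest that treatment works differently across patient groups.

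**5. Do the allegiance remedies reach the analysis?** Supervision, the adherence scale and the manuals all act on delivery of therapy. None acts on model choice or reporting.

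**Result.** Steps 1 and 2 put training and analysis in one group. Step 3 finds no stated masking, step 4 finds real discretion in two places, and step 5 finds no remedy that covers it.

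**The case against.** The strongest reply is that this argues from silence. A journal article condenses a fuller protocol, and the named analyst and any masking are often left to the analysis plan. That stands in part: the absence of a masking statement is not itself an error. What does not depend on silence is the role assignment, which the article makes, and the answer to its own question about who is blinded.

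A reader might infer three stronger things that the document does not support.

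- **That the analysts see the arms.** Nothing says so.
- **That the ASSIP trainers do the analysis, or hold an allegiance.** A shared subgroup does not establish either, and {17b} refers separately to a statistician.
- **That a false-positive rate can be attached.** Inflation from choosing the best of several tests arises for any analyst, neutral or masked. It would also need correlations between tests that the document does not give. It measures the lack of one primary model, not allegiance.

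It is also fair to say that the discretion is limited. The log-rank test needs no covariate choice, the selection thresholds are stated, and anyone holding the data can repeat the test. This narrows the route but does not close it, because the reported model and the plausible interactions remain open.

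**Conclusion.** The point holds as an unguarded route for bias, not as a demonstrated bias. ASSIP training and data analysis sit in one subgroup, stated blinding stops at outcome assessors, and part of the primary analysis is decided on the trial data. The protocol recognises therapy allegiance as a threat but counters it only for therapists.

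The size of any bias is unknown. The conclusion assumes that the full protocol or analysis plan does not already separate the roles or code the arms; if it does, only the article's role wording needs correcting.

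Masking would not remove the freedom to choose among models. It would stop that freedom from being used in a known direction. Naming one primary model is a separate matter.

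**What to change.** 1. Amend the International collaborators entry so that nobody who provides ASSIP training analyses the primary or secondary outcomes. The collaborators keep training and dissemination.
2. Add the data analyst to {17a} as masked, working from a file with arms coded A/B/C until the model is fixed and the primary estimates are produced.
3. Have the biostatistician in {16c} apply and hold the code. Having generated the allocation list, that person cannot reliably be masked and should not be the masked analyst. An existing team member who does not hold the list should analyse. This assumes that the team includes someone suitable.

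Step 2 is needed as well as step 1. The article says the research team adapted the CBT manual, so moving the analysis without coding the arms could exchange one possible allegiance for another. The coded file should omit fields that reveal the arm, such as sessions attended (three for ASSIP, six for CBT).

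The cost is a change of wording, a coded file to prepare, and a short delay before results are seen by named arm. Trial status reports 12 of the planned 411 participants recruited, so at that stage the change could be made before most outcome data existed.

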##### ASSIP-CBT Working Group (subgroup)

Study planning, referral pathways, advice for lead investigators, quality assurance, treatment as usual pathway, and clinical intervention procedures.

##### Research Clinical Supervision Group and MDT meetings (subgroups)

Training, supervision, all subgroups report to the steering committee. This study was formally monitored by the Gold Coast Health Office for Research Governance and Development - Clinical trials monitoring officer (see section 23).

#### Composition of the data monitoring committee, its role, and reporting structure {21a}

No Data Safety Monitoring Board has been appointed for this study. The study is considered low risk by HREC, and care is as per current Gold Coast Health guidelines for consumers, which already follows a leading postvention model (the SPP). The ASSIP-CBT steering committee provides oversight on the ongoing conduct, safety, and progress of the trial.

#### Adverse event reporting and harms {22}

All adverse events (reported and observed) will be reported to HREC, and recorded by the research team, with respect to any of the following types of harm occurring in the study, and the likelihood, severity, and consequence of those harms occurring.

